## Abstract

**Background:**

A vaginal fistula is a devastating condition, affecting an estimated 2 million girls and women across Africa and Asia. There are numerous challenges associated with providing fistula repair services in developing countries, including limited availability of operating rooms, equipment, surgeons with specialized skills, and funding from local or international donors to support surgeries and subsequent post-operative care. Finding ways of providing services in a more efficient and cost-effective manner, without compromising surgical outcomes and the overall health of the patient, is paramount. Shortening the duration of urethral catheterization following fistula repair surgery would increase treatment capacity, lower costs of services, and potentially lower risk of healthcare-associated infections among fistula patients. There is a lack of empirical evidence supporting any particular length of time for urethral catheterization following fistula repair surgery. This study will examine whether short-term (7 day) urethral catheterization is not worse by more than a minimal relevant difference to longer-term (14 day) urethral catheterization in terms of incidence of fistula repair breakdown among women with simple fistula presenting at study sites for fistula repair service.

**Methods/Design:**

This study is a facility-based, multicenter, non-inferiority randomized controlled trial (RCT) comparing the new proposed short-term (7 day) urethral catheterization to longer-term (14 day) urethral catheterization in terms of predicting fistula repair breakdown. The primary outcome is fistula repair breakdown up to three months following fistula repair surgery as assessed by a urinary dye test. Secondary outcomes will include repair breakdown one week following catheter removal, intermittent catheterization due to urinary retention and the occurrence of septic or febrile episodes, prolonged hospitalization for medical reasons, catheter blockage, and self-reported residual incontinence. This trial will be conducted among 512 women with simple fistula presenting at 8 study sites for fistula repair surgery over the course of 24 months at each site.

**Discussion:**

If no major safety issues are identified, the data from this trial may facilitate adoption of short-term urethral catheterization following repair of simple fistula in sub-Saharan Africa and Asia.

**Trial registration:**

ClinicalTrials.gov Identifier NCT01428830.

## Background

A vaginal fistula is a devastating condition, and while true prevalence is unknown, it is estimated to affect 2 million girls and women across Africa and Asia. The primary cause of a vaginal fistula is prolonged obstructed labor: the fetus's head compresses the soft tissues of the bladder, vagina and rectum against the woman's pelvis, cutting off blood supply to the tissue, causing the tissue to die and slough away. The result is an abnormal opening between the vagina and bladder, or between the vagina and rectum, or both, and either urinary and/or fecal incontinence.

Approximately 80-95% of vaginal fistula can be closed surgically [1]; however, the provision of fistula repair services in developing countries is not without challenges. Specialized training and skills are necessary, especially to handle more complex cases, and this limits the availability of services. Women with fistula are predominantly poor and from rural areas, and often cannot pay for surgery or transport to a service site. Thus, fistula repair services must be provided free of charge. Fistula services are few and far between in Africa and Asia: the availability of services depends not only on the availability and motivation of surgeons with specialized skills, but also the availability of operating rooms, equipment, and funding from local or international donors to support both surgeries and lengthy post-operative care. In most contexts, the need for repair services exceeds the available human and infrastructural capacity. Moreover, the prolonged bladder catheterization that is frequently employed after surgery translates into a need for longer hospitalization, more intensive nursing care, and increased costs, leading to decreased capacity for treating other patients. Longer duration catheterization may also be associated with increased risk of healthcare-associated infection. Reducing the duration of bladder catheterization, provided no compromise in surgical outcomes and patient health, has important implications for the delivery of fistula care and treatment services in low resource settings.

Bladder catheterization practices following fistula repair and other pelvic surgery vary. Publications about fistula surgery often state that bladder drainage through indwelling urethral catheterization should continue between 10 and 14 days post-operatively [2,3]. However, in both fistula repair [4] and other types of gynecological surgery [5], the duration of bladder drainage via indwelling urinary catheter is primarily based on custom rather than empirical research, and the duration of drainage varies substantially. A recent survey of 40 fistula surgeons conducted by Arrowsmith and colleagues [6] found that catheterization durations following fistula repair surgery ranged from 5 to 21 days, with 13% of surgeons reporting they catheterize women for 8 days or less following surgical repair of simple fistula. Results from a multi-country prospective cohort study examining predictors of repair outcomes recently completed by Fistula Care/USAID also found a wide distribution in post-repair duration of urethral catheterization among 1274 women. The median duration of catheterization was 21 days, with an interquartile range (IQR) of 14-27 days [7]. A wide range has also been found for duration of catheterization following colovesical fistula repair. A retrospective review of data at Massachusetts General Hospital conducted by de Moya and colleagues found that duration of catheterization following colovesical fistula repair secondary to diverticulitis ranged from 3-42 days [8]. While colovesical fistula repairs differ considerably from vaginal fistula repairs, these findings nonetheless indicate that not only is shorter-term catheterization currently being implemented for different types of bladder surgery, but that it may be a feasible alternative to longer term catheterization following the repair of simple urinary fistula in women.

Short-term urethral catheterization may in fact pose no additional risk to patients in terms of repair prognosis. One purpose of post-repair urethral catheterization is to provide an opportunity for adequate tensile strength to develop so that bladder distension does not disrupt the healing wound. The presumption behind prolonged catheterization is that the bladder heals better "at rest" (i.e. when it is not filling and emptying); however, there is little evidence to support this. For non-contaminated wound healing in general, the critical period involving granulation and neovascularization peaks at 5 days and inflammation is over in 1 week [9], with matrix deposition and cell proliferation continue until at least 30 days. Tensile strength increases rapidly during the first 5 days, although final tensile strength is not reached until over 100 days. A recent study evaluating the effects of long-term catheterization on extracellular matrix (ECM) biological scaffold remodeling following partial cystectomy in canines, found that early bladder filling (i.e. shorter duration of catheterization) mediated a constructive remodeling response [10]. While biologic scaffolds composed of ECM are a cutting edge innovation not feasible for fistula repair in developing countries, these results suggest that removing the catheter early and allowing the bladder to begin filling and emptying, may be beneficial, rather than harmful, to bladder healing. Nonetheless, no basic physiologic studies on the dynamics of wound healing in the bladder after fistula repair have been published to date and it is possible that the wound healing process following fistula repair may be more prolonged than noted above given the contaminated and chronic nature of most vaginal fistula.

Given the potential benefits of short-term urethral catheterization, and the fact that it is currently being practiced by some fistula surgeons, empirical evidence is needed to determine the non-inferiority of short-term urethral catheterization compared to longer-term urethral catheterization. The primary objective of this study is thus to examine whether short-term (7 day) urethral catheterization is not worse by more than a minimal relevant difference to longer-term (14 day) urethral catheterization in terms of incidence of fistula repair breakdown among women with simple fistula.

## Methods/Design

This will be a non-inferiority randomized controlled trial (RCT) comparing the new proposed short-term (7 day) urethral catheterization to longer-term (14 day) urethral catheterization in terms of predicting fistula repair breakdown, measured 3 months following fistula repair surgery. This study will be conducted among 512 women with simple fistula presenting at eight study sites for fistula repair surgery (Table 1). Figure 1 depicts the flow of study participants.

**Table 1 T1:** Study sites

Country	Site
Democratic Republic of Congo	Hôpital Saint Joseph de Kinshasa

Ethiopia	Gondar University Hospital Fistula Unit

Guinea	Prefectural Hospital of Kissidougou

Kenya	Kenyatta National Hospital

Niger	Maternité centrale de Zinder

Nigeria	National Obstetric Fistula Centre Abakaliki

Sierra Leone	Aberdeen Women's Centre

Uganda	Kagando Hospital

**Figure 1 F1:**
[figure not shown]
**Trial profile**. Women who consent to participate in the study may be determined ineligible prior to randomization: (1) at the time of surgery if the surgeon determines that the fistula is 'not simple': (2) at the end of surgery if the fistula is not closed based on dye test results; and (3) 7 days after surgery if the fistula is not closed based on dye test results. Seven days after surgery, women with a closed fistula will be randomized to catheter removal on that day (i.e. the 7-day removal group) or to have the catheter kept in place for an additional 7 days (i.e. the 14-day removal group). Women will remain at the study site for an additional 7 days after catheter removal. On days 1, 3 and 7 after catheter removal, urine retention will be assessed and intermittent catheterization employed as needed. Women with a positive urinary dye test at 7 days following catheter removal will be classified as having experienced a repair breakdown and their participation in the study will be completed. Remaining women will be asked to return for a follow-up visit 3 months after the date of surgery.

### Intervention

The study intervention will entail removal of the urethral catheter at 7 days after surgery in the intervention arm and 14 days after surgery in the control arm. While 7 and 14 days are the target days for urethral catheter removal in the two groups, should it be necessary to remove the catheter either one day earlier or one day later (e.g. holiday, surgeon unavailable) in either group (i.e. 6-8 days or 13-15 days) these women will still be considered as compliant with the group assignment. Each patient will receive the same type of catheter, and with the exception of the timing of catheter removal, all other procedures related to the removal of the catheter will remain the same across both study arms. No drugs or new devices will be examined as part of this study.

### Outcome measures

The primary study endpoint is fistula repair breakdown any time after day 7 after urethral catheter removal up to three months following surgery. Repair breakdown will be assessed using a dye test; a urinary catheter will be inserted into the bladder, saline colored with dye will be introduced into the bladder via the catheter, and the suture line will be checked for leaks.

Secondary outcomes will include: repair breakdown one week following indwelling urethral catheter removal, the need for intermittent catheterization to manage urinary retention, and the occurrence of septic or febrile episodes, prolonged hospitalization, catheter blockage, and self-reported residual incontinence. Prolonged hospitalization will be defined as a stay at the facility beyond one week following initial catheter removal for medical reasons.

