### Study population

All women who present at study sites for fistula repair surgery will be potentially eligible. Women will be randomized if:

• they have a "simple" fistula, based on the surgeon's perception during surgery

• they have a closed fistula at completion of surgery

• they have a closed fistula 7 days after surgery

• they understand study procedures and requirements

• they agree to return to the facility for one follow-up visit three months after the date of surgery

• they provide informed consent to participate in the study

• they have no contraindications precluding their participation

Women will be excluded if they have a fistula that is:

• determined to be "not simple"

• radiation-induced, associated with cancer or due to lymphogranuloma venereum

• not closed immediately after surgery or 7 days after surgery

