### Analysis plan

The primary outcome of the trial is repair breakdown at 3 months or earlier in an intent-to-treat (ITT) analysis. The primary analysis will be conducted for the ITT population. The ITT population would include patients for whom the protocol is violated (i.e. patients who are randomized to short-term catheterization but are in fact catheterized for longer durations, or patients who are randomized to the long-term catheterization group but are in fact catheterized for only 7 days) and withdrawals.

Unlike a superiority trial, where the treatment effect is the primary parameter of interest, the interpretation of a non-inferiority trial's results depends on the location of the CI for the effect of the experimental treatment relative to the margin of non-inferiority (Δ) and a null effect. A range of possible scenarios are depicted in Figure 2, where error bars indicate 2-sided 95% CIs, and the tinted area indicates the zone of inferiority. Thus, primary analyses will be interpreted as follows: if the whole 95% CI lies to the right of the non-inferiority margin of 10% (scenario H), the experimental intervention will be declared "inferior." If the whole 95% CI lies below the non-inferiority margin, the intervention will be considered to be non-inferior to the standard treatment (scenarios B-D). If the 95% CI includes the non-inferiority margin Δ (scenarios E, F and G) study results will be deemed inconclusive. Finally, in scenario A, since the 95% CI lies completely to the left of zero, the new treatment may be considered superior to the standard treatment [11].

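### The Outcome measures section starts the primary endpoint only after day 7 following catheter removal, which contradicts the abstract and the Analysis plan and could favour non-inferiority

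*Protocol article*

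**What the plan says.** The article describes the primary endpoint in three places.

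- Outcome measures: "The primary study endpoint is fistula repair breakdown any time after day 7 after urethral catheter removal up to three months following surgery".
- Abstract, Methods/Design: "The primary outcome is fistula repair breakdown up to three months following fistula repair surgery as assessed by a urinary dye test".
- Analysis plan: "The primary outcome of the trial is repair breakdown at 3 months or earlier in an intent-to-treat (ITT) analysis".

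Outcome measures also names a secondary outcome: "repair breakdown one week following indwelling urethral catheter removal".

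The trial profile (Figure 1 legend) says how an early failure is handled: "Women with a positive urinary dye test at 7 days following catheter removal will be classified as having experienced a repair breakdown". These women then leave the trial, and only the others are asked back at 3 months: "their participation in the study will be completed. Remaining women will be asked to return for a follow-up visit 3 months after the date of" (the date meant is that of the operation).

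To be randomized, women must meet the condition that "they have a closed fistula 7 days after surgery". Any breakdown in the trial is therefore a breakdown after randomization.

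The sample size section takes its 13% control failure rate from a cohort of 145 women with simple repairs, of whom 87% had a closed fistula at 3 months.

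**The concern.** The definition in Outcome measures has a late start that the abstract and the Analysis plan lack. Under its wording, a woman whose repair has failed by the dye test one week after removal is a breakdown in the trial profile but not a primary event. Because her participation ends there, she cannot become a primary event later. With one-week breakdown listed as secondary in the same section, a reader can take the two outcomes as separate, non-overlapping windows.

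In a non-inferiority trial, leaving out failures matters when they are unevenly spread between arms. The Background says the catheter protects the healing wound from bladder distension, and filling resumes at removal. The first week after removal is therefore a plausible time for any harm from early removal to appear, although the documents give no timing of breakdowns. If an excess in the 7-day arm did fall in that week, the literal endpoint would hide some or all of it from the comparison that decides the trial. Two incompatible primary definitions also leave room to choose between them after the data are seen.

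**Working it through.** **Step 1. Which definition fits the rest of the article?**

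| Section | What it implies for a positive test one week after removal |
|---|---|
| Outcome measures | Not a primary event, read literally |
| Abstract, Methods/Design | Primary event (no late start) |
| Analysis plan | Primary event (3 months or earlier) |
| Trial profile | A repair breakdown, and participation ends; primary endpoint not named |
| Sample size | Failure rate taken from closure status at 3 months, so early failures that persist are included |

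The opening of Methods/Design says only that breakdown is measured 3 months after surgery. That does not settle the matter either way.

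**Step 2. Reproduce the sample size.** Inputs from the sample size section: 13% failure in both arms, margin 10 points, one-sided α 0.025, power 80%.

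n per arm = 2 × 0.13 × 0.87 × (1.960 + 0.842)² / 0.10² = 177.5

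The article states 177. Inflating for 30% in total: 2 × 177.5 / 0.70 = 507, as stated. The trial is thus sized on the cumulative 3-month rate. An endpoint limited to late breakdowns would have a lower rate. If half of control breakdowns fell in the first week, for instance, it would be 6.5%, and 96 per arm would be enough.

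**Step 3. Effect of the late start on the decision.** Assumptions, none of them given in the documents:

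- True cumulative breakdown is 23% (7-day) and 13% (14-day), an excess of 10 points, exactly at the margin.
- The late control rate is 6.5%, so half of control breakdowns are early.
- A share s of the 10-point excess falls in the first week after removal.
- Early failures stay in the denominator as non-events.
- 177 women per arm are analysed.

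Late rate in the 7-day arm: p₇ = 0.065 + 0.10 × (1 − s). Late rate in the 14-day arm: p₁₄ = 0.065. Difference: d = p₇ − p₁₄.

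SE = √{[p₇(1 − p₇) + p₁₄(1 − p₁₄)] / 177}

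P(non-inferior) = Φ[(0.10 − d)/SE − 1.96]

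Counting all breakdowns, d = 0.10, so P = Φ(−1.96) = 2.5%, the nominal error rate. Under the literal endpoint:

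| s | p₇ | d | SE | P(non-inferior) |
|---|---|---|---|---|
| 0% | 16.5% | 0.100 | 0.0335 | 2.5% |
| 25% | 14.0% | 0.075 | 0.0320 | 11.9% |
| 50% | 11.5% | 0.050 | 0.0303 | 37.8% |
| 75% | 9.0% | 0.025 | 0.0284 | 75.2% |
| 100% | 6.5% | 0.000 | 0.0262 | 96.8% |

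**Step 4. Sensitivity to the denominator.** The article does not say how early failures would be treated under the literal endpoint. Suppose they are removed from the denominator and s = 100%. The 14-day rate is 0.065/0.935 = 7.0% of 165.5 women, and the 7-day rate is 0.065/0.835 = 7.8% of 147.8. Then d = 0.0083, SE = 0.0296 and P = Φ(0.0917/0.0296 − 1.96) = 87%. At s = 0% the same calculation gives 1.6%. The result still depends mainly on s.

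**The case against.** The strongest reply is that this is loose wording and not the plan. The abstract, the Analysis plan, the trial profile and the sample size all point to a cumulative endpoint, against one sentence. After randomization, the article describes dye tests only one week after removal and at 3 months, so the sentence may be meant to describe ascertainment from the one-week test onward. With from in place of after, the conflict would be gone. Listing one-week breakdown as secondary does not remove it from a cumulative primary. An early excess would also not go unseen, because it is a named secondary outcome and the DSMB guideline on breakdowns carries no late start.

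Most of this stands. It makes a drafting error the likelier explanation, and a reader who infers that the trial means to leave out early failures goes further than the documents allow. It does not clear the sentence. Outcome measures is the formal definition, and a secondary outcome does not decide non-inferiority.

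A reader might also infer that early removal will cause first-week breakdowns. The documents do not show this. The Background says that shorter catheterization may pose no added risk and that evidence for resting the bladder is slight. Examples that put the whole excess in the first week show only the worst case.

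Nor is it a separate fault that the literal window opens about day 14 after surgery in one arm and day 21 in the other. The one-week test falls on those days by design.

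**Conclusion.** The contradiction is real and lies in the primary endpoint. As worded, Outcome measures excludes breakdowns found up to and including day 7 after catheter removal, against the abstract and the Analysis plan, and it does not fit the trial profile or the basis of the sample size.

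The direction of the risk is conditional: the literal endpoint favours non-inferiority if excess breakdown in the 7-day arm occurs in the first week after removal. Its size rests on the assumed share. With true rates at the margin and early failures as non-events, the false non-inferiority rate runs from 2.5% (none of the excess early) to about 97% (all of it early). A quarter of the excess is enough to raise it to about 12%. No single figure in that range can be taken from the documents.

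The sentence must be corrected, because it could change the trial's conclusion and the remedy is small.

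**What to change.** Replace the sentence in Outcome measures so that it agrees with the abstract and the Analysis plan. Suggested wording: *The primary endpoint is repair breakdown (positive dye test) at any time from randomization, 7 days after surgery, up to 3 months after surgery, including a positive test at or before 7 days after catheter removal.*

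Keep one-week breakdown as a secondary outcome. The abstract and the Analysis plan need no change.

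The cost is a one-sentence amendment. It needs no extra visits, data or patients. The sample size stays as it is, since the 13% already refers to status at 3 months.

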### Random allocation technique and allocation concealment

Allocation of the random generated sequence will be by consecutively numbered envelopes. Allocation concealment will be achieved by using sealed opaque envelopes. Allocation will take place 7 days after fistula repair surgery.

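### Breakdown one week after catheter removal counts failures over 7 days since randomization in one arm and 14 in the other, so comparing the arms on it favours early removal if any repairs fail with the catheter in place

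*Protocol article*

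**What the plan says.** All places are in the Protocol article.

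- **Common start.** To be randomized, women must satisfy "they have a closed fistula 7 days after surgery" (Study population). "Allocation will take place 7 days after fistula repair surgery" (Random allocation technique and allocation concealment). The Figure 1 legend agrees: "Seven days after surgery, women with a closed fistula will be randomized to catheter removal on that day", or to keep it for a further 7 days.
- **Removal.** The intervention is "removal of the urethral catheter at 7 days after surgery in the intervention arm and 14 days after surgery in the control arm" (Intervention). One day either side still counts as compliant.
- **Outcome.** The first secondary outcome is "repair breakdown one week following indwelling urethral catheter removal" (Outcome measures). The Figure 1 legend says how it is read: "Women with a positive urinary dye test at 7 days following catheter removal will be classified as having experienced a repair breakdown".
- **Procedures at removal.** Timing apart, "all other procedures related to the removal of the catheter will remain the same across both study arms" (Intervention). No dye test at the day-14 removal is described for the control arm.
- **Primary outcome.** The Abstract and the Analysis plan describe breakdown at any time up to 3 months after surgery. Outcome measures instead starts the count after the seventh day following removal.

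**The concern.** Both arms start from the same negative dye test on day 7, but the next described test is tied to removal and comes a week later in the control arm. A control repair that fails between days 7 and 14, with the catheter in place, is counted. A 7-day-arm repair that fails between days 14 and 21 is not. The control arm is therefore charged with an extra week of failures.

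The tilt is towards the regimen the trial hopes to support. The Discussion makes adoption conditional on no major safety issue being found, and an early breakdown result would naturally be read beside the 3-month result as safety evidence. It could show an early advantage where none exists, or mask a modest early excess.

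**Working it through.** **1. The plan's own figure.** The document gives no figure for this outcome, so the sample size is the check on the inputs. With 13% failure in both arms, a 10% margin, one-sided 0.025 and 80% power:

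n = 2 × 0.13 × 0.87 × (1.960 + 0.842)² / 0.10² ≈ 177.5 per arm, against 177 stated. Then 2 × 177.5 / 0.70 ≈ 507, as stated, and 8 × 64 = 512, or about 256 per arm.

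**2. The windows.**

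| | 7-day arm | 14-day arm |
|---|---|---|
| Closed test and randomization | day 7 | day 7 |
| Removal | day 7 | day 14 |
| One-week test | day 14 | day 21 |
| Days since randomization | 14 − 7 = 7 | 21 − 7 = 14 |

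The one-day tolerance on removal moves the tests to days 13-15 and 20-22. The windows stay unequal.

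**3. What drives the bias.** Let c be the risk of failure on catheter between days 7 and 14, and q the risk in the week after removal, taken as equal in both arms. The 7-day arm shows q. The 14-day arm shows 1 − (1 − c)(1 − q). The difference is −c(1 − q), which is zero if c = 0 and otherwise favours the 7-day arm.

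**4. Size.** The document gives no data on when repairs fail, so the timing is assumed. Let a proportion F of women break down between day 7 and day 90 (83 days), with the same timing in both arms.

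- Constant hazard: λ = −ln(1 − F)/83. With F = 13%, λ = 0.001678 per day. Day 14: 1 − exp(−7λ) = 1.17%. Day 21: 1 − exp(−14λ) = 2.32%.
- Front-loaded with half-life h days: the proportion failed t days after day 7 is F(1 − 0.5^(t/h)) / (1 − 0.5^(83/h)), read at t = 7 and t = 14.

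The chance of a nominally significant result favouring the 7-day arm is Φ(d/SE − 1.96), where d is the size of the difference, SE = √[p₁(1 − p₁)/256 + p₂(1 − p₂)/256], and p₁ and p₂ are the two proportions. For F = 13% and constant hazard, d = 0.01154 and SE = 0.01156, giving Φ(−0.96) ≈ 17%. Exact enumeration of a pooled two-sided 5% z-test gives 15%.

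| F | Timing | 7-day arm | 14-day arm | Difference (points) | Chance (normal / exact) |
|---|---|---|---|---|---|
| 13% | constant | 1.2% | 2.3% | −1.2 | 17% / 15% |
| 13% | h = 14 | 3.9% | 6.6% | −2.7 | 29% / 28% |
| 13% | h = 7 | 6.5% | 9.8% | −3.3 | 27% / 27% |
| 13% | h = 2 | 11.9% | 12.9% | −1.0 | 5% / 5% |
| 10% | h = 2 | 9.1% | 9.9% | −0.8 | 5% / 5% |
| 15% | h = 7 | 7.5% | 11.3% | −3.8 | 31% / 31% |
| 15% | h = 14 | 4.5% | 7.6% | −3.2 | 32% / 32% |

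Over F = 10-15% and all timings tried, the spurious difference runs from −0.8 to −3.8 points and the chance from about 5% to 32%, against 2.5% for an unbiased comparison.

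**The case against.** **Anchoring on removal is deliberate.** It gives each arm 7 catheter-free days, which fits the Background's account of the catheter protecting the repair from distension. A common day-21 reading would compare 14 catheter-free days with 7. This stands as a reason to keep the outcome. It does not equalise the time over which failures since randomization are counted.

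**The full protocol may include a control dye test on day 14.** The sentence on equal removal procedures can be read that way, although the day-7 test is also an eligibility test. Such a test would not repair the comparison. A failure found then is either counted, which leaves the window at 14 days, or left out, which removes failures from one arm only.

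**No formal test of this outcome is stated.** This is correct. The Analysis plan describes testing only for the primary outcome. The 5-32% says what would happen if the arms were compared in the usual way, not what the protocol commits to.

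**Larger effects are tempting.** A reader might infer that doubled time means doubled failures. That holds roughly only under constant hazard. If most failures come within days of day 7 the ratio is near one (11.9% against 12.9%). A reader might also assume 2-4% failure per week, which would give false-favourable chances of 26-46%. Continued to day 90, those rates imply 1 − 0.98^(83/7) = 21% to 1 − 0.96^(83/7) = 38% breakdown, against the 10-15% the protocol expects. The trial also excludes women whose repair is open on day 7, so later failure may be rarer still.

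**A reader might infer that the trial's main conclusion is biased.** As defined in the Abstract and the Analysis plan, the primary outcome runs from a common randomization day to a common 3-month visit and is not affected. That cannot be said of the wording under Outcome measures, which starts on day 14 or day 21 and leaves 90 − 14 = 76 or 90 − 21 = 69 days.

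**Conclusion.** The concern holds as a minor point about one secondary outcome. The windows of 7 and 14 days since randomization follow directly from the stated schedule. The direction, towards early removal, follows if any repairs fail on catheter. The size does not come from the document: about 1 to 4 percentage points, and a 5-32% chance of a nominally significant false advantage, rest on no true effect, 256 women per arm with complete data, 10-15% failure by day 90 and assumed timing curves that are the same in both arms. If no repair fails on catheter, there is no bias. The non-inferiority decision is untouched, provided that the cumulative definition of the primary outcome is the one used.

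**What to change.** 1. Under Outcome measures, state that breakdown one week after removal is reported descriptively by arm, with the day after surgery of the test, and is not used as comparative evidence that early removal is safe.
2. Base between-arm claims about breakdown on the cumulative outcome from randomization to 3 months after surgery, as in the Abstract and the Analysis plan.
3. Align the primary endpoint sentence under Outcome measures with that definition, so that its start does not depend on the removal day.

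An early endpoint at day 21 built on recalled onset of leakage is not a good substitute. Control failures up to day 21 would be found by dye test at the site. Failures on days 14-21 in the 7-day arm would be found only if the woman returned at 3 months (the sample size allows 20% loss) and dated the onset correctly. That would undercount the 7-day arm and restore the same bias.

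The cost is two or three sentences, with no added procedure or form. What is lost is a formal comparison at equal catheter-free time.
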